### Specific Aim #2

Using narrative analysis techniques as suggested by Cortazzi [32] the journals will be analyzed to describe the participants' perception of what fosters their hope from the journals. Data will be organized into three major structural categories that describe: 1) the event, 2) experience, and 3) evaluation by participants. From these categories themes describing what fosters their hope will emerge.

### Specific Aim #3

Hypothesis #3.1 (patterns of GSE, RGEI/NGREGI, HHI, SF12 and HSU over time) will be tested by repeated measures 2- factor ANCOVA with between groups factor (non-bereaved versus bereaved) and a repeated-measures factor for time (3, 6, and 12 months) to describe the patterns of the scores over time. PPS and caregiver demographics that were significantly correlated will be co-variants. If the F scores are significant (p < .05) post hoc testing will be done to determine where the scores are significantly different.

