### Specific Aims and Hypotheses

Table 1 outlines the operationalization of the study concepts (measures) based on the LWHP conceptual model. The research team based the decisions for the variables being studied on the LWHP conceptual framework. We also considered which measures could be used given that subjects would become bereaved and minimal burden of data collection to all subjects was a chief consideration.

**Table 1 T1:** Variables and Measures

Variables	Caregivers/measures	Bereaved Caregivers/measures
Hope	Herth Hope Index (HHI)	Herth Hope Index (HHI)

Self Efficacy	General Self Efficacy Scale (GSE)	General Self Efficacy Scale (GSE)

Grief/Loss	Non Death Version of the Revised Grief Experience Inventory (ND RGEI)	Revised Grief Experience Inventory (RGEI)

Quality of Life	Short Form 12 Quality of Life Questionnaire Version 2 (SF12) Palliative Performance Scale (PPS) for family member with advanced cancer	Short Form 12 Quality of Life Questionnaire Version 2(SF12)

Health Services Utilization	# of physicians visit and prescriptions one year after study enrolment minus one year prior.	# of physicians visit and prescriptions one year after study enrolment minus one year after.

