### Specific Aim #1

To determine the mechanisms of the LWHP by testing the LWHP conceptual model (Figure 1), by examining if, at 1 and 2 weeks post LWHP compared to baseline, self-efficacy [General Self-Efficacy Scale (GSE)] and Loss and Grief [Revised Grief Inventory (RGEI) or NonDeath RGEI (NDRGEI)] scores predict changes in hope [Herth Hope Index (HHI) Factor 1] and quality of life [SF12 V2 mental health sub score-MHS (MHS-SF12)] scores for rural women caring for persons with advanced cancer.

1.1 Main Hypothesis: The subjects' general self efficacy and loss and grief (RGEI/NDRGEI) scores will significantly predict the HHI (Factor 1) score and the mental health score on the SF12 V2 at 1 and 2 weeks.

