Sample Size: Sample size has been determined based on the requirements of the statistical methods that will be used to test the hypotheses and approximation of subject attrition rates. Path Analysis is the statistical analysis for the main hypothesis of testing the LHWP at week one and two. According to Munro [26] sample size and power calculations for Path Analysis can be made using Cohen's formulation for the most complex regression equation in the Path model. Thus, for a power of 0.80, and an alpha of 0.05, a regression equation, including 6 variables [general self efficacy, loss/grief, hope (factor1), quality of life (mental health sub score), and health services utilization (physician visits and prescriptions)] would require 98 subjects. As the study progresses, caregivers will become bereaved. The exact time and percentage of caregivers who will be bereaved is unknown. Based on Saskatoon Health Region Palliative Home Care data in the year 2001-2002, the average length of stay for palliative patients is 70 days (2.3 months) with 25% dying in 13 days, 50% in 36 days and 75% in 82.75 days. This means that approximately 50% of the subjects may become bereaved in a little over a month. In order to have sufficient numbers of subjects in both groups (active and bereaved caregivers) the sample size will be doubled to 200. Two hundred subjects would provide adequate power for the proposed analysis, so sampling will continue until this is achieved.

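### Health services utilization is defined only as a year-before/year-after count, so it fits neither the 3/6/12-month ANCOVA nor the week-1/2 regression behind 98; its Table 1 entry for bereaved caregivers is also a slip

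*Protocol article*

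**What the plan says.** **Definition of HSU.** The abstract, Purpose, the aims text for Specific Aim #3 and Methods/Design all describe HSU as a comparison of the year before with the year after enrolment or the program. Methods/Design says the data are obtained this way for all subjects. The measures it repeats at 1 and 2 weeks and at 3, 6 and 12 months are hope, quality of life, loss/grief and self-efficacy; HSU is not among them.

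**Table 1 (Specific Aims and Hypotheses).** For active caregivers the measure is the year after enrolment minus the year prior. For bereaved caregivers it is the number "of physicians visit and prescriptions one year after study enrolment minus one year after".

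**Analysis of Aim 3 (Data Analysis, Specific Aim #3).** "Hypothesis #3.1 (patterns of GSE, RGEI/NGREGI, HHI, SF12 and HSU over time) will be tested by repeated measures 2- factor ANCOVA", with bereavement status as the between-groups factor and 3, 6 and 12 months as the repeated factor. Hypothesis 3.1 as worded in the aims names GSE, RGEI/NDRGEI, HHI and SF12 only; change in HSU is to be described.

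**Sample size (Setting and Sample).** "Path Analysis is the statistical analysis for the main hypothesis of testing the LHWP at week one and two". The number comes from "Cohen's formulation for the most complex regression equation in the Path model": "for a power of 0.80, and an alpha of 0.05, a regression equation, including 6 variables", and the list of six runs from general self-efficacy through "loss/grief, hope (factor1), quality of life (mental health sub score), and health services utilization (physician visits and prescriptions)] would require 98 subjects". Hypothesis 1.1, the main hypothesis, says only that self-efficacy and loss/grief scores "will significantly predict the HHI (Factor 1) score and the mental health score on the SF12 V2 at 1 and 2 weeks". No effect size is given. The total is then doubled to 200 to allow for active and bereaved groups.

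**The concern.** One variable with a single two-year window is used in three places that need something different.

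- A repeated-measures model with levels at 3, 6 and 12 months needs a value at each level. HSU supplies one difference, or two annual counts, per subject.
- The Table 1 entry that operationalizes HSU for bereaved caregivers is not a before/after comparison at all, and bereaved against active is the contrast of Aim 3.
- The regression that justifies 98 belongs to weeks 1 and 2. The post-enrolment year of HSU is not complete then, and Hypothesis 1.1 does not contain HSU.

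At stake are whether the HSU part of Aim 3 can be carried out as stated, and whether the published 98 matches the model it is meant to support.

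**Working it through.** **1. ANCOVA against the data definition.** The time factor has three levels. The HSU definition yields (count in year after) − (count in year before), which is one number per subject. No count is defined for any interval ending at 3, 6 or 12 months, so the factor cannot be filled. The aims text does not ask for it either: Hypothesis 3.1 there omits HSU. The conflict therefore lies between the analysis section for Aim 3 and the rest of the article.

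**2. Table 1.** Active: after − prior. Bereaved, as printed: after − after = 0 for every subject. Methods/Design gives the prior and after windows for all subjects, so the intended entry is clearly after − prior.

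**3. The 98.** Inputs from Setting and Sample: alpha 0.05, power 0.80, six variables. Effect size: not stated; f2 = 0.15 is assumed.

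Method: F test of R² against 0 with u predictors, v = N − u − 1 error degrees of freedom and noncentrality λ = f2 × N. Power is the probability that a noncentral F(u, v, λ) exceeds the 95th percentile of the central F(u, v).

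Reproducing the plan's figure with u = 6: at N = 98, v = 98 − 6 − 1 = 91 and λ = 0.15 × 98 = 14.7, giving power 0.804. At N = 97 power is 0.798. The smallest N is therefore 98, as stated.

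Other predictor counts at f2 = 0.15:

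| Predictors | What they could be | N for 80% power | Power at 98 |
|---|---|---|---|
| 2 | self-efficacy, loss/grief | 68 | 0.932 |
| 3 | plus hope, in the quality-of-life equation | 77 | 0.898 |
| 4 | plus PPS | 85 | 0.866 |
| 5 | – | 92 | 0.834 |
| 6 | all six listed variables | 98 | 0.804 |

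At this f2 only u = 6 gives 98. All six listed variables are then counted as predictors: both HSU variables, and also hope and quality of life, which are the outcomes in Hypothesis 1.1. PPS and the demographic covariates that the Aim 1 analysis intends to include are not in the list.

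Sensitivity to the assumption: with u = 6, f2 = 0.02 would need 688 and f2 = 0.35 would need 46. Fewer predictors could also give 98 at another f2 (for example u = 2 at about 0.101), but the document names six variables, and six at 0.15 reproduces the number exactly.

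**4. Effect on the planned 200.** Doubling 68, 77 or 85 gives 136, 154 or 170, all below 200. In the other direction, if covariates brought the total to 10 or 15 predictors (illustrative; the document gives no count), the requirement at f2 = 0.15 would be 118 or 139. Power with all 200 subjects would be 0.98 or 0.95.

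**The case against.** Four points can be made for the plan.

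- **The Table 1 entry is a typing slip that Methods/Design resolves.** This stands. A reader might infer that the plan would report no change in bereaved caregivers by construction. The document does not support that, because the prior and after windows are stated for all subjects and no analyst would subtract a year from itself. The cell still has to be corrected.
- **HSU is a descriptive element of Aim 3.** This stands in part. The aims text says so, and the four scales in Hypothesis 3.1 are unaffected. But the analysis section says HSU will be tested in the ANCOVA, so the two sections must be aligned.
- **HSU may be a node of the path model.** Background places it downstream of quality of life, and Figure 1 is not shown. The final variable set also depends on observed correlations. It would therefore be too strong to say that 98 fits no equation the team might fit. What remains is that HSU cannot be observed at weeks 1 and 2 and is absent from Hypothesis 1.1.
- **There is no loss of power.** This stands. A reader might infer an underpowered study, since 10 or 15 predictors at N = 98 would give power of 0.69 or 0.58. Those covariate counts come from no document, and 98 is not the planned enrolment.

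One might also object that a single annual difference mixes active and bereaved time. At the quoted median of 36 days, a caregiver would be bereaved for (365 − 36)/365 = 90% of the after year. That concerns how finely to describe HSU and is not a contradiction in the text. A before/after difference compared by group is coarse but answers the stated aim.

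**Conclusion.** The point holds as an internal inconsistency with a cheap correction. The 3/6/12-month ANCOVA of HSU cannot be run on HSU as defined, and it conflicts with Hypothesis 3.1 in the aims. The bereaved entry in Table 1 is literally zero and is evidently a slip. The figure of 98 counts two HSU variables that do not belong to a week-1/2 test of Hypothesis 1.1; without them the same method gives 68, 77 or 85, depending on whether two, three or four predictors are counted.

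These numbers rest on the assumed f2 of 0.15, which reproduces 98 but is not stated. Counting HSU makes the number larger, and nothing here shows that 200 is too few for the whole-sample path model. The ANCOVA conclusion assumes that no interval counts of HSU are planned; dated administrative records might allow them, but the article defines none.

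**What to change.** 1. In the analysis of Aim 3, remove HSU from the repeated-measures ANCOVA, so that it agrees with Hypothesis 3.1 in the aims. Analyse physician visits and prescriptions as annual counts before and after enrolment, compared by bereavement group, with a count model. If the administrative extract carries dates, interval counts split at the date of death may be added.
2. In Table 1, change the bereaved entry to one year after minus one year prior, as for active caregivers.
3. In the sample-size paragraph, restate the predictor count without HSU and without the equation's own outcome, count the covariates to be fitted (PPS and demographics), state f2, and give the resulting number.

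The cost is wording in the analysis plan and one table cell. No additional subjects or data collection are needed; only the optional interval counts depend on dated records, which the article does not describe.

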## Discussion

Data collection for this study began January 2009. Since that time there have been changes to the initial study protocol. On a monthly basis data collectors and site collaborators meet with the PI to discuss recruitment and data collection procedures. These meetings have been instrumental in identifying recruitment and data collection problems. It has resulted in clarification of inclusion criteria and data collection procedures and suggestions for additional sites for recruitment. For example, the study was initially to have been conducted at the Saskatchewan Cancer Agency. Additional rural health region sites have been added when recruitment was not progressing as planned in the first year of the study. Although the Cancer Agency serves the province, persons with advanced cancer appear to be in contact with their home care or palliative home care nurses more frequently then the primary oncology nurses.

In one of the recruitment meetings the data collectors identified the H1N1 pandemic as effecting study recruitment. The data collectors and site collaborators have been assigned additional duties as part of the pandemic response that resulted in their inability to focus on the study for recruitment. Although this resulted in a 3 month delay, the study timeline is for three years with data collection occurring over 28 months.

The work of the research team in conjunction with clinicians and terminally ill patients and families has resulted in a promising and practical psychosocial supportive hope program that may improve the quality of life of growing numbers of Canadians. Psychosocial issues in cancer are potentially crippling [33]. Over 200, 000 people die in Canada each year with their deaths affecting the well-being of an average of five other people [34]. Family care giving is what sustains patients at the end of life [35] and with changing demographics and diminishing resources there is a potential that every Canadian will be an informal caregiver at some time [36]. The LWHP is a unique and innovative approach to support family caregivers.
